#### Analysis

2.14.2

A predefined statistical analysis plan will be followed. All statistical analyses were conducted with IBM SPSS (version 21.0). *P* values of <.05 were considered to represent statistical significance. Categorical variables would be reported as counts and percentages. The mean and standard deviation or median with interquartile ranges (IQR) were used to describe continuous variable data, as appropriate.

The primary analysis is a comparison between ENGBD and PTGBD for the pain remission based on an intention-to-treat principle. A multilevel, random-slope model would be fitted to the data with time points nested in patients to allow for clustering of data within each patient. This model adjusted for the fixed effects of treatment group, time (−2, 24, 48 , or 72 hours), and treatment × time interaction. An unstructured covariance pattern was selected for the repeated measurements as the least restrictive structure, which resulted in better model fit based on log-likelihood values than more constrained patterns. Estimates of the difference in pain scores between treatment groups were assessed overall and at individual time points.

The secondary analysis is a comparison between ENGBD and PTGBD for the rates of technical and clinical success, adverse events, and changes in the gallbladder wall thickness . Also, the outcomes during cholecystectomy including time duration, open conversion would also be analyzed. The Chi-square test or Fisher exact test was used for dichotomous variables, and Wilcoxon test was used for rank data. For quantitative data, two-tailed Student *t* test is used, if the normal distribution and homogeneous total variance are satisfying, otherwise, Wilcoxon test is used.

A blinded adjudication committee will assess the occurrence of the primary and secondary endpoints after the last patient has completed follow-up.

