#### Primary outcome measures

2.8.1

The primary outcome is the pain score, defined as pain experienced during mobilization from the supine to the standing position. Using the visual-analogue scale, pain score would be obtained within 2 hours before drainage and at post-drainage 24, 48, and 72 hours in conscious and communicating patients by a specially trained nurse, who devoted herself to the objectivity and authenticity of the scores. The details of assessment are as follows: draw a 10-cm line on a piece of paper, mark one end of the line with the number 0, indicating no pain; the other end with 10, indicating the most severe pain; the middle part indicates different degrees of pain. While assessing the pain of patients, make sure the patient could not see the numbers on the paper and let them mark the position according to their feelings about the pain. Then the nurse would get a score based on the mark. Pain scores reflect directly the degree of pain, the remission of pain not only relieves the pain symptoms associated with acute cholecystitis itself, but also relatively alleviates the severe pain caused by tube.

In order to avoid the effects of anesthesia, we chose to evaluate the pain 24 hours after drainage. Especially, all pain assessments should be performed without the administration of pain killers or after using an analgesics for 6 hours. All modifications in pain management are recorded. Our team routinely prepares a multimodal approach to pain management, which is applied mainly based on nonsteroidal anti-inflammatory drugs and other adjuvant drugs, but tries to avoid applying it.

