### Sample size

2.10

The sample size calculation is based on the primary outcome-the pain score after drainage. According to the research by Jang et al,^[18]^ using the method provided by Luo et al^[19]^ and Wan et al,^[20]^ the median post-procedure pain score in the PTGBD group was 5.4 ± 3.1. And the mean visual analog score of post-procedure pain in the ENGBD group was 1.3 by Itoi et al.^[9]^ Using a theoretical sample size for two-sample design, nine participants are needed in each group with 80% power and a 5% significance level. Allowing for a 10% loss to follow-up, we plan to recruit 22 patients (11 in each group).

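### The primary pain analysis counts the pre-drainage score as an outcome time and names no deciding contrast; on the natural reading of the overall difference, a quarter of the post-drainage effect is averaged away

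*Protocol article*

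**What the plan says.** Primary outcome measures (2.8.1): "pain score would be obtained within 2 hours before drainage and at post-drainage 24, 48, and 72 hours in conscious and communicating patients". So there is one score before treatment and three after it, and no hour is named as primary.

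Analysis (2.14.2): "The primary analysis is a comparison between ENGBD and PTGBD for the pain remission based on an intention-to-treat principle". The multilevel model has "fixed effects of treatment group, time (−2, 24, 48 , or 72 hours), and treatment × time interaction". No baseline covariate is named, and the arms are not constrained to a common mean at −2 h. The results are described as "Estimates of the difference in pain scores between treatment groups were assessed overall and at individual time points". The only significance threshold given is P below .05, for all analyses. The section also refers to a predefined statistical analysis plan, which is not shown.

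Sample size (2.10): the trial is sized on a single post-procedure score, with no hour given: "the median post-procedure pain score in the PTGBD group was 5.4 ± 3.1", against a mean of 1.3 for ENGBD. This gives nine per group, raised to 11 per group (22 in total) for loss to follow-up.

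**The concern.** Allocation is random and the −2 h score precedes drainage, so the expected group difference at that time is zero. An overall difference averaged over all four times therefore mixes three treatment effects with one quantity that treatment cannot affect. The estimate shrinks towards zero and the test loses power.

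The pre-drainage score would be more useful as a covariate. In that role it removes between-patient variation, and the text as printed forgoes this gain.

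Separately, the overall estimate and the individual-time estimates stand side by side under one threshold. A reader of the results could not tell from this text which of them was meant to decide the trial.

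**Working it through.** **Inputs.** From Sample size: PTGBD 5.4, SD 3.1; ENGBD 1.3; 80% power; 5% significance; 9 per group analysed, 11 recruited. The difference is d = 5.4 − 1.3 = 4.1. Assumed, because the protocol does not give them: SD 3.1 in both arms and at every time, equal correlation ρ between any two times (0.3, 0.5, 0.7), and a constant effect at 24, 48 and 72 h.

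**The plan's own figure.** n = 2 × [3.1 × (1.960 + 0.842) / 4.1]² = 8.97, so 9 per group, two-sided. The stated figure is reproduced.

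**Dilution.** Equal-weight average over the four model times: (0 + 4.1 + 4.1 + 4.1) / 4 = 3.075. Ratio to 4.1: 0.75, so a quarter is lost.

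**Effect on power.** A quarter off the estimate is not a quarter off the power, because averaging also reduces the SD. With complete data and a free mean for each arm and time, the overall contrast is a two-sample t test on each patient's average.

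- SD of the four-time average: 3.1 × √[(1 + 3ρ)/4] = 2.14, 2.45, 2.73 for ρ = 0.3, 0.5, 0.7.
- SD of the 24–72 h average: 3.1 × √[(1 + 2ρ)/3] = 2.26, 2.53, 2.77.
- Noncentrality: difference / (SD × √(2/n)). Example for n = 11, ρ = 0.5: 3.075 / (2.45 × 0.426) = 2.94 for the four-time average, and 4.1 / (2.53 × 0.426) = 3.80 for the post-drainage average.

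Two-sided 5% power from the noncentral t distribution (covariate row by simulation):

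| Contrast, 11 per arm | ρ = 0.3 | ρ = 0.5 | ρ = 0.7 |
|---|---|---|---|
| Average of −2, 24, 48, 72 h | 89% | 80% | 71% |
| Average of 24, 48, 72 h | 98% | 95% | 91% |
| Same, −2 h score as covariate | 99% | 99% | 99.9% |

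With 9 per arm, the four-time average has 82, 71 and 61%, and the 24–72 h average without a covariate has 95, 90 and 84%.

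The first two rows differ only by removing −2 h from the contrast. The step to the third row is the gain from the covariate, a separate matter.

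**Several contrasts at .05.** Simulated with no true effect and 11 per arm, the chance that the overall contrast or at least one of the three post-drainage contrasts reaches p < .05 is 15, 13 and 11% at ρ = 0.3, 0.5 and 0.7. One named contrast keeps it at 5%.

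**The case against.** **The overall difference is not defined.** It could mean a joint test of treatment by time, with −2 h as the reference. The stated target of pain remission, a change from before drainage, gives that reading some support. There would then be no dilution. This stands as a limit on the 25% figure. Against it, the sentence speaks of estimates of a difference in scores, which a joint test does not supply, and on that reading the deciding contrast would still be unnamed.

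**Baseline among the outcomes is a legitimate model.** Agreed. A reader might infer that omitting the adjustment biases the post-drainage comparisons. It does not: under randomisation they are unbiased, only less precise. The weakness lies in averaging over baseline and in not using it to gain precision.

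**The power gap can be overstated.** Setting 71–89% against 99% merges two changes, dropping −2 h and adding a covariate. With 11 per arm, even the diluted test is at or close to the planned 80% for ρ of 0.5 or less. The correlations are assumed, and equal correlation is simpler than the unstructured pattern the protocol specifies.

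**The two harms do not add up.** A reader might infer that the trial loses power and inflates its error at the same time. If the four-time overall test alone decides, power falls but the error stays at 5%. If any contrast may be claimed, the error rises but most of the power returns (about 95 to 98% with 11 per arm at 4.1 points).

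**Linear time.** The random-slope wording might suggest that the treatment term is the difference at hour 0, close to pre-treatment. The text never says that this term would be the test. It lists four times and promises an estimate at each, which points to categories.

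**The analysis plan may settle it.** It may well name the contrast and deal with the several time points, so their absence from an article is weak evidence on its own. But the article does state the time levels, the fixed effects and the form of the results, and those are what need tightening.

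**Conclusion.** The point holds as a should-fix, free improvement. As printed, the primary analysis includes the pre-drainage score among the outcome times, does not adjust for it, and does not say which contrast decides.

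On the natural but undefined reading of the overall difference as an equal-weight four-time average, with a constant post-drainage effect, 4.1 points becomes 3.08. With 11 per arm, leaving −2 h in the contrast costs about 9, 15 and 20 percentage points of power at correlations of 0.3, 0.5 and 0.7. With the 9 per arm on which the trial is sized, power is below 80% at correlations of 0.5 and 0.7. A free choice of contrast would instead put the false-positive rate at about 11 to 15%.

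The documents do not support saying that the analysis is invalid, that the post-drainage comparisons are biased, or that dilution is certain.

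**What to change.** Define the primary contrast in Analysis as the mean ENGBD–PTGBD difference over 24, 48 and 72 h. Use the pre-drainage score either as a covariate, with the three post-drainage scores as outcomes, or as an outcome with both arms constrained to a common mean at −2 h. Test this one contrast once, at two-sided .05. Report the differences at 24, 48 and 72 h with confidence intervals, labelled supportive. If the analysis plan already fixes this, align the wording here with it.

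The cost is a few sentences. All four scores are already scheduled, so no patients, visits or measurements are added.

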#### Collection, management

2.14.1

All data are prospectively collected and managed by the well-trained research volunteers.

The baseline data would be collected and registered on inclusion: age, sex, body mass index (BMI), body temperature, interval between onset of AC and drainage, comorbidities and coexisting conditions, american society of anesthesiologists (ASA) grade, charlson comorbidity index (CCI), AC grade based on TG 18 severity grading,^[4]^ white blood cell (WBC) count, electrolytes, total bilirubin, C-reactive protein (CRP), and so on. This would systematically reflect the characteristics of participants.

The peri-drainage data would be obtained from 2 hours before drainage to one week after ENGBD or PTGBD, such as drainage success, clinical remission, adverse events, pain scores within 2 hours before drainage and at post-drainage 24 h, 48 h, 72 h, etc.

The following data are collected and registered on peri-LC: gallbladder wall thickness changes (pre-drainage to pre-LC), duration and hemorrhage of LC, gallbladder integrity, drainage tube, hospitalization (hospital stay after gallbladder drainage and cholecystectomy), surgical site infection, severe adhesion, pathology, and LC-related complications.

Results that are negative or undetected or measured as 0 should have corresponding symbolic representation and can not be vacant, in order to distinguish from missing values. The treatment of outliers should be judged from both medical and statistical aspects by the statistician during blind examination.

Images and biological samples including venous blood and bile will be collected for probably ancillary and long-term research. Also, all patients will be followed up 6 months after cholecystectomy.

The volunteers of data acquisition have rich clinical experience and rigorous working attitude, and received training and guidance. Data storage would be carried out by two independent investigators to ensure reliability and validity.

We would also pay attention to and collect the information of the participants who discontinue or deviate before cholecystectomy and the follow-up are completed. To promote participants’ retention and enthusiasm, we would establish workflow manuals contact patients regularly, communicate properly and take effective care of their health.

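### The change in gallbladder wall thickness is compared without baseline adjustment; ANCOVA on the pre-drainage value already collected would usually be modestly more precise

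*Protocol article*

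**What the plan says.** Section 2.14.1 (Collection, management) of the protocol article lists among the data gathered around laparoscopic cholecystectomy (LC) "gallbladder wall thickness changes (pre-drainage to pre-LC". Each patient analysed therefore has a starting value and a later value.

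Section 2.14.2 (Analysis) names "changes in the gallbladder wall thickness" as a between-group secondary comparison. For quantitative data it prescribes a two-tailed Student t test "if the normal distribution and homogeneous total variance are satisfying, otherwise, Wilcoxon test is used". It mentions no covariate for any secondary outcome. The only model that handles pre-treatment values jointly with later ones is the repeated-measures model for pain: "This model adjusted for the fixed effects of treatment group, time" and their interaction, with the pre-drainage time point included. The general significance rule is that P "values of <.05 were considered to represent statistical significance".

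The same section refers to a predefined statistical analysis plan, which is not shown. Table 1, which details the secondary outcomes, is not shown either.

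**The concern.** A patient's change from baseline is normally correlated with the baseline itself: a wall that starts unusually thick tends to thin more, partly through regression to the mean. A t test on the change subtracts the whole starting value, as if each extra millimetre at baseline carried over in full to the pre-LC measurement. When the true carry-over is smaller, a chance difference between arms in starting thickness is over-corrected, and the surplus enters the estimated treatment difference as noise.

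With 11 patients per arm, chance differences of a noticeable size are common and precision is scarce. Estimating the slope from the data, as ANCOVA does, usually removes this noise. What is at stake is the width of the confidence interval for one secondary outcome.

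**Working it through.** **The plan's own figure.** No sample size is stated for wall thickness. The only calculation is for pain (section 2.10): "the median post-procedure pain score in the PTGBD group was 5.4 ± 3.1", "the mean visual analog score of post-procedure pain in the ENGBD group was 1.3", and "nine participants are needed in each group with 80% power and a 5% significance level". Taking 3.1 as the common SD and a difference of 5.4 − 1.3 = 4.1, the normal approximation gives n = 2 × (1.96 + 0.84)² × (3.1/4.1)² ≈ 9 per arm, which reproduces the stated figure. The article then plans 22 patients, 11 per arm. Only that number is carried forward.

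**Inputs.**
- n = 11 per arm, N = 22 (section 2.10).
- Correlation r between pre-drainage and pre-LC thickness: not in the documents; assumed 0.3 to 0.7, with 0.9 as an extreme.
- SD s equal at both times: assumed.

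**Variances**, leaving out the common factor 2/n:
- change score: 2s²(1 − r)
- ANCOVA, slope known: s²(1 − r²)
- ratio: (1 + r)/2

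Estimating the slope multiplies the ANCOVA variance by about 1 + 1/(N − 4) = 19/18 = 1.056. The interval-width ratio is the square root of the adjusted variance ratio, times the ratio of t quantiles on 19 and 20 degrees of freedom.

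| r | (1 + r)/2 | × 19/18 | 95% CI width, ANCOVA ÷ change score |
|---|---|---|---|
| 0.3 | 0.65 | 0.69 | 0.83 |
| 0.5 | 0.75 | 0.79 | 0.89 |
| 0.7 | 0.85 | 0.90 | 0.95 |
| 0.9 | 0.95 | 1.00 | 1.005 |

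Over r = 0.3 to 0.7 the variance falls by 10 to 31% and the interval narrows by about 5 to 17%. With 9 analysed per arm the factor is 15/14 and the variance ratios are 0.70, 0.80 and 0.91, so modest losses to follow-up do not alter the picture.

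**Simulation check** (normal data, equal variances, 40,000 runs per setting, 11 per arm). The simulated variance ratios were 0.69, 0.80 and 0.90 for r = 0.3, 0.5 and 0.7. Power for an assumed difference of 1 SD, change score against ANCOVA, was 0.47 against 0.62, 0.61 against 0.71, and 0.82 against 0.85. Type I error was about 0.05 for both.

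**Where the loss comes from.** The baseline mean difference has SD √(2/11) = 0.43 baseline SDs and exceeds 0.5 SD in either direction with probability about 24%. Given an imbalance of 0.5 SD, the change-score estimate is displaced by (1 − r) × 0.5 SD: 0.35, 0.25 or 0.15 SD at r = 0.3, 0.5 or 0.7. The excess variance of the change score is 2(1 − r) − (1 − r²) = (1 − r)² in units of s², that is 0.49, 0.25 and 0.09. This is exactly the variance contributed by that displacement. Imbalance and lost precision are one quantity seen from two sides.

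**The case against.** The strongest reply is that nothing here is wrong. The change score does use the baseline, randomisation makes the comparison unbiased, and the test holds its level. All of that stands. A reader might infer that the plan ignores chance baseline imbalance, or that its comparison is biased. The documents do not support this: the outcome as collected subtracts each patient's own starting value, and the standard error already covers the resulting variation. Nor is imbalance a second harm on top of lost precision, as the last step of the working shows. It would also be too strong to say that a change score can never be the more precise choice, because at this sample size the two methods are level near r = 0.9.

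A second reply is that the analysis plan may settle covariates, that the test rule is generic and does not name wall thickness, and that the exact definition of the change (absolute, percentage or categorised) may lie in the missing table. The last point limits what can be checked. But the article does more than stay silent: it names the comparison and fixes an unadjusted test for quantitative data, and an analysis plan that follows it inherits the choice.

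A third reply is that wall thickness matters little. Section 2.2 describes cholecystectomy difficulty through grading, duration and pathology, and sections 2.14.1 and 2.14.2 list many other operative outcomes. This also stands and sets the weight of the point.

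**Conclusion.** The point holds as a modest efficiency improvement to one secondary outcome. With 11 per arm, ANCOVA would reduce the variance of the wall-thickness comparison by about 10 to 31% if the pre/post correlation lies between 0.3 and 0.7, and by nothing if it is near 0.9.

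The size rests on three assumptions: that range of correlations, equal variances at the two times, and a change defined as a simple difference. None can be verified from the documents. Section 2.7 places surgery 3 months after drainage so that inflammation can settle. This makes a modest correlation plausible but does not give a value. The primary pain analysis and the number of patients are unaffected.

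**What to change.** In section 2.14.2, or in the analysis plan before data are examined, state that pre-LC gallbladder wall thickness will be analysed by ANCOVA with treatment arm as factor and pre-drainage thickness as covariate, and that the adjusted difference will be reported with its 95% confidence interval. Keep the unadjusted change per arm as a descriptive summary.

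If a non-parametric analysis is wanted, prespecify it as a sensitivity analysis and do not switch method after looking at the residuals. A rank-based analysis would not directly give the adjusted thickness difference.

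The cost is one sentence and one degree of freedom. Both measurements are already planned, so no new data are needed.

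### The test for each quantitative secondary outcome is picked from the data, and the rule misses the .05 level for a comparison of means when variances and analysed group sizes both differ (minor)

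*Protocol article*

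**What the plan says.** Section 2.14.2 (Analysis) sets one rule for all quantitative secondary outcomes. It begins "For quantitative data, two-tailed Student" t test and makes that test conditional: "if the normal distribution and homogeneous total variance are satisfying, otherwise, Wilcoxon test is used". Every failure of either condition, including unequal variance alone, leads to Wilcoxon. No check, threshold or unequal-variance t test is named. The same section states that P "values of <.05 were considered to represent statistical significance".

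The outcomes concerned include those listed in section 2.14.1, such as "gallbladder wall thickness changes (pre-drainage to pre-LC), duration and hemorrhage of LC", and hospital stay. Section 2.14.2 itself names wall-thickness change and operative duration.

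On size, section 2.10 says "nine participants are needed in each group with 80% power and a 5% significance level" and plans 22 patients, 11 per arm, to allow for 10% loss. Section 2.3 gives 1:1 allocation.

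**The concern.** The rule has three weaknesses.

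- **Low power of the checks.** At about 11 per arm, a check of equal variance often passes when variances differ. The pooled-variance t test is then kept where it should not be.
- **Wrong remedy.** When unequal variance is found, the plan moves to Wilcoxon. That test is itself sensitive to unequal spread and can reject too often or too seldom when means and medians are equal.
- **Shifting question.** The result is a comparison of means or of ranks, and which one is settled only after the data are in.

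The conditions for trouble are plausible here, though not documented. Cholecystectomy follows drainage by 3 months (section 2.7), and section 2.14.1 foresees patients leaving before it, so operative outcomes may be analysed in unequal numbers. If outcomes are analysed as randomised, the ENGBD arm may also include patients given a fallback procedure (section 2.7). The Discussion cites 81% pooled technical success for ENGBD. Such a mixture could make that arm more variable, but this is an inference.

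At stake is the reliability of P values for outcomes such as operative time, which bear on the trial's interest in the later cholecystectomy.

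**Working it through.** **Step 1: arm sizes.** Section 2.10 gives means of 5.4 and 1.3 (difference 4.1) and an SD of 3.1. The 3.1 is stated for PTGBD only and is assumed common to both arms. With two-sided .05 and 80% power, the normal approximation gives

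n = 2 × (1.960 + 0.842)² × 3.1² / 4.1² = 8.97, so 9 per arm.

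This reproduces the plan's figure. Allowing for 10% loss, 9 / 0.9 = 10 per arm; the plan takes 11. Losing 10% of 22 leaves 22 × 0.9 = 19.8, about 20 patients. If both losses fall in one arm, the sizes are 11 v 9. A split of 11 v 7 means 4 of 22 (18%) lost, all from one arm.

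**Step 2: the rule, simulated.** Assumptions: Shapiro-Wilk in each arm and mean-centred Levene, each at .05; Student t if all pass, otherwise exact Wilcoxon rank-sum; normal data with equal means; 20,000 trials per case (standard error about 0.15 to 0.2 points). The protocol gives no SD for any secondary outcome, so the SD ratios are assumed.

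Type I error, nominal 5%. Where two figures appear, they are for SD ratio 2 / 3:

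| Sizes | Equal SDs | Larger SD in smaller arm | Larger SD in larger arm |
|---|---|---|---|
| 11 v 11 | 5.0% | 5.5% / 5.7% (sizes equal) | same |
| 11 v 9 | 5.3% | 6.3% / 7.0% | 4.2% / 4.3% |
| 11 v 7 | 5.4% | 7.7% / 9.2% | 3.0% / 2.9% |

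Repeat runs gave up to 7.9% at 11 v 9 and 8.1% to 8.9% at 11 v 7 with the larger SD in the smaller arm. Hence the rounded ranges of 4% to 8% and 3% to 9%.

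**Step 3: why it happens.**
- At a true SD ratio of 2, Levene rejected in 46% of trials at 11 v 11, in 39% to 43% at 11 v 9 and in 32% to 40% at 11 v 7.
- At 11 v 7 and SD ratio 2, with the larger SD in the smaller arm, Student t was kept in 53% of trials. Its error in those trials was 10.6%.
- Wilcoxon used alone at 11 v 7 and SD ratio 3 gave 8.8% or 3.8%, depending on direction. Moving to it does not restore the level.

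**Step 4: the alternative.** Welch's t test, fixed in advance, gave 4.6% to 5.3% on normal data in these same cases, and up to 5.7% in a repeat run. With equal variances, 11 v 11 and a true difference of 1.2 SD, its power was 76.8%, against 76.2% for the plan's rule.

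**Step 5: skewed data.** With lognormal data of the same shape in both arms (log-scale SD 0.5), the plan's rule gave 4.4% to 4.7% and Welch 3.9% to 4.2%.

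**The case against.** The case on the other side is substantial, and most of it stands.

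- **Unequal sizes alone do no harm.** A reader might infer that the .05 level fails as soon as group sizes differ. It does not: with equal SDs the rule gave 5.0% to 5.4% from 11 v 9 down to 11 v 6. Unequal variance is needed as well, and the error can then be too low as easily as too high.
- **Little happens at the planned design.** At 11 v 11 the excess is under 1 point, and at 9 v 9 the rule gave 4.9% to 5.1%. The larger figures need lopsided losses and an SD ratio of 2 or 3, which no section documents.
- **A fully null treatment is safe.** If the procedures did not affect an outcome at all, both arms would share one distribution, and the rule holds its level there. The distortion concerns equal means with different spread.
- **Formal checks are inferred.** The article does not say how the conditions are judged. A separate analysis plan may say, and the statistician is masked, which limits selective choice. The branching itself, and Wilcoxon as the answer to unequal variance, are stated in the article.
- **The reach is limited.** Drainage success, remission and adverse events are dichotomous, and difficulty grading is rank data already assigned to Wilcoxon.
- **The fix is partial.** Wilcoxon remains sensitive to unequal spread for the outcomes assigned to it.

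These points lower the severity. They do not make the rule a good one, because a better test named in advance costs almost nothing.

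**Conclusion.** The point holds in a limited form. For quantitative secondary outcomes, the rule in section 2.14.2 does not hold .05 for a comparison of means when variances and analysed group sizes both differ. The level is then about 4% to 8% at 9 v 11 and about 3% to 9% at 7 v 11. This rests on Shapiro-Wilk and Levene checks at .05, normal data and an SD ratio of 2 to 3, none of which the protocol states. With equal variances, or at 11 v 11, the level stays within about 1 point of 5%. Apart from the level, the quantity compared depends on the data.

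The severity is minor. The documents do not support reading this as a threat to the trial's main conclusion, because pain score is analysed with a multilevel model that does not use this rule.

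**What to change.** In section 2.14.2, replace the conditional rule with one test per quantitative secondary outcome, named before data are seen:

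- Welch's t test, with the mean difference and 95% CI, for roughly symmetric outcomes such as operative time and wall-thickness change.
- The Wilcoxon rank-sum test, interpreted as a comparison of distributions rather than means, for outcomes expected to be skewed, for example blood loss and hospital stay.
- No choice of test based on normality or variance checks.

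The cost is one sentence of wording, with no new patients or data and no loss of power under equal variances. There are two downsides. Welch is conservative for skewed data (3.9% to 4.2% in the lognormal runs above), which is why skewed outcomes go to Wilcoxon. A Wilcoxon result may still reflect a difference in spread and should be reported with that caution.
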